### Statistical analysis

Descriptive statistics will be reported as mean and standard deviation for normally distributed continuous variables, or median with interquartile range in the case of skewed distribution. An intention-to-treat analysis will be performed on all randomized subjects to provide unbiased comparisons among groups and avoid the effects of dropout. Study outcomes will be measured as changes from baseline to all assessment points (6-, 12-, 18-month). Changes will be tested with linear mixed models, which account for repeated measures collected in a longitudinal design and deal better with dropouts, without the need for imputation of missing data. Intraclass correlations coefficients will be also reported to take into account the potential correlation among individuals within group. Statistical analyses will be performed with IBM SPSS Statistics.

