### Randomization and data collection

Randomization will be web-based, stratified by sex, age, and PA level at baseline to obtain homogeneity between study groups. All data collected from the participants will be handled via REDCap (Vanderbilt University, US), a secure web platform specifically geared to support online and offline data capture for research studies. The randomization sequence will be concealed from the study team by the program. Neither study participants nor data analysts will be blinded to group allocation.

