#### Peer support via social media

Participants in group C will be invited to join a Facebook closed-group. The aim of this group is to provide a platform for participants to share their experiences, ask for advice, support or motivation from peers, and discuss technical or practical challenges. The project team, as administrators, will provide general information and educational advice about PA, motivational support, rewarding messages, technical and practical help. This, in turn, might prevent dropouts.

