### Outcome measures

The primary outcome is the average time spent in moderate and vigorous PA. Objective measurement of PA will be undertaken using the ActiGraph GT3X+ accelerometer worn at the right hip by each participant for eight consecutive days. The ActiGraph GT3X+ should be taken off when showering or bathing. A day of data will be included if there are at least 10 h of data. A minimum of four valid days of data will be required (36). Total physical activity will be measured as total acceleration counts per minute in triaxal vector magnitude (square root of the summed activity counts from all three axes) counts per minute. The intensity of PA will be split by acceleration cut-off of <150 triaxial counts per minute (sedentary time), 150–2,689 triaxial counts per minute for light and >2,690 triaxial counts per minute for moderate and vigorous PA (37, 38), which are calibrated to correspond to <1.5, 1.5–2.9 and 3.0 metabolic equivalents of tasks (METs).

The proportion of participants reaching the recommendation for PA will be measured, for each group, at all time points (Table 1). Longitudinal changes will express a measure of maintenance of long-term adherence to exercise. The proportion of participants reaching the goal of 100 PAI/week will also be measured for the entire duration of the study.

**Table 1 T1:** Schedule of enrolment, interventions, and assessments.

**Time point**	**Enrolment**	**Baseline**	**6-month**	**12-month**	**18-month**

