The lack of social support is another common barrier to PA (10). Poor adherence to home-based exercise (24), in addition to the poor adherence observed in e-health interventions (51), makes the implementation of digital technologies for PA a challenging issue. Novel strategies are needed to ensure adherence to PA among adults and maintenance of behavior change (27). Social media are nowadays widely used in many people's daily routines and are shown to be valuable for targeting lifestyle change among young adults (28). In a study examining the efficacy of a Facebook social support group to increase PA in young women, participants in a Facebook social support group increased the number of steps per day more than those in the standard walking intervention (30). Participants in group C will be offered peer support *via* a Facebook closed-group, where they will have the possibility to share their experiences or ask for advice from other members of the group, as well as receive educational information about PA, motivational support and rewarding messages from the project team. It is expected that peer-support *via* social media will result in better adherence to PA, better maintenance of PA levels over the long-term, as well as fewer dropouts.

This study can contribute to reduce disparities in PA levels among inactive adults by increasing access to PA and promoting long-term adherence. Increased PA might, in turn, result in better prevention of lifestyle diseases. Digital interventions delivered at home can become an alternative to training facilities, making PA accessible and feasible for inactive populations and overcoming known barriers to PA. If effective, such interventions could potentially be offered on a large-scale through national health portals to all citizens who do not meet the minimum recommendations on PA. Effective e-health interventions for PA could also be prescribed by general practitioners or specialists to both healthy and impaired individuals. The study will be conducted in the Troms and Finnmark county in Northern Norway. However, the results will be applicable to other regions and countries. The interventions could be also applicable to selected patient groups, particularly those with mobility impairment characterized by low levels of PA.

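### The plan says intention-to-treat on all randomised participants avoids the effects of dropout; its change-score model without imputation cannot deliver this, and fewer dropouts are expected in group C

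*Protocol article*

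**What the plan says.** Three statements in the Statistical analysis section of the protocol article belong together.

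- Population and claim: "An intention-to-treat analysis will be performed on all randomized subjects to provide unbiased comparisons among groups and avoid the effects of dropout".
- Response: "Study outcomes will be measured as changes from baseline to all assessment points (6-, 12-, 18-month".
- Model: "Changes will be tested with linear mixed models, which account for repeated measures collected in a longitudinal design and deal better with dropouts". The sentence adds that no imputation is needed.

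Elsewhere the article predicts that retention will depend on arm. Peer support goes to group C only. Of the Facebook group and the project team's support, the section on peer support says "This, in turn, might prevent dropouts". The Discussion expects peer support to bring "better maintenance of PA levels over the long-term, as well as fewer dropouts". The Sample size section allows for 10% attrition overall and gives no split by arm. Under Outcome measures, an accelerometer record counts only with at least four valid days of at least 10 hours each.

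**The concern.** The claim promises something the analysis does not have. Intention-to-treat fixes the comparison groups and says nothing about outcomes that were never observed. The mixed model does handle dropout better than a complete-case analysis, but only when missingness can be explained by data already in the model. Two features of this plan strain that condition.

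1. If the change itself is the response, a participant without a valid follow-up record has no response. That person's baseline value, although observed, is not used, so the analysis set is not everyone randomised. For everyone else, the baseline level enters only through the difference and cannot explain later dropout.
2. The intervention in group C is expected to reduce dropout. If less active people are also the ones who leave, the arms lose different kinds of participant, and the C contrast on the primary outcome absorbs part of that.

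A reader of the article would take the between-arm comparison to be protected from dropout, when its validity rests on an unstated assumption.

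**Working it through.** **Inputs from the article.** 180 participants, 60 per group; attrition 10% overall; correlation between measures 0.5; d = 0.53; power 0.80; alpha 0.05 (two-sided assumed); assessments at baseline, 6, 12 and 18 months.

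**The plan's own figure.** n per group = 2 × (1.96 + 0.842)² / 0.53² = 55.9, so 56. With r = 0.5 the SD of a change is √(2 × (1 − 0.5)) = 1 raw SD, so the change-score calculation also gives 56. Inflating for loss, 56 / 0.90 gives 63, slightly above the planned 60. With 54 completers per group (60 × 0.90) power is 0.786, close to the stated 0.80. The sample size is not at issue here.

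**How many have no response under the literal reading.**

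- All attrition before month 6: 180 × 0.10 = 18 lost, 162 analysed.
- Attrition spread evenly over three visits: loss before the first follow-up = 1 − 0.90^(1/3) = 3.5%; 180 × 0.0345 ≈ 6 lost.
- At an assumed 18-month loss of 15% in A and 5% in C, evenly spread: about 5.3% of A and 1.7% of C have no change score, or roughly 3 and 1 of 60.

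**Bias in the 18-month C minus A contrast.** The article gives neither dropout rates by arm nor a mechanism, so both are assumed. Large-sample simulation: 200,000 per arm, four visits, all correlations 0.5, unit SD, no true difference between arms, monotone dropout. The log-odds of leaving rise by 1.0 for each SD of lower activity. Loss by month 18 is set at A/C = 15/5%, 30/10% and 40/15%. The first split averages to the planned 10%.

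| Dropout depends on | Model | 15/5% | 30/10% | 40/15% |
|---|---|---|---|---|
| Observed earlier activity (missing at random) | Change scores, no baseline term | +0.03 | +0.06 | +0.08 |
| Observed earlier activity (missing at random) | Baseline as response or covariate | ≈ 0 | ≈ 0 | ≈ 0 |
| Unobserved current activity (not at random) | Change scores, no baseline term | −0.01 | −0.04 | −0.05 |
| Unobserved current activity (not at random) | Baseline as response or covariate | −0.03 | −0.08 | −0.10 |
| Nothing (completely at random) | Either | ≈ 0 | ≈ 0 | ≈ 0 |

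Figures are in SD units. Equal loss of 10% in both arms also gives about zero under every mechanism.

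**Scale.** 0.03 / 0.53 = 6% and 0.08 / 0.53 = 15% of the planned effect size. The largest not-at-random value is 0.10 / 0.53 = 19%.

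**Why the signs differ.** People with low observed activity tend to rise towards the mean at the next visit. Losing more of them from A lowers A's mean change and flatters C; once baseline is in the model, this regression is accounted for. When people leave because their current, unseen activity is low, A's surviving mean is too high and C looks worse. No term built from observed data fully repairs that. Unadjusted change scores show less bias in this case only because the two errors partly cancel.

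**The case against.** The strongest reply is that the change-score reading is not the only one. The text speaks of repeated measures in a longitudinal design, which also fits a model of activity at every visit with change estimated as a group-by-time contrast. On that reading everyone with a valid baseline stays in, and the comparison is valid under missing at random. This is fair. The article does not say which model is meant, and the loss of participants and the +0.03 to +0.08 SD apply only to the literal one. The unconditional claim about dropout is wrong on either reading.

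A second reply is that the numbers are small and assumed. That also stands: unequal dropout alone causes no bias, and at a split consistent with 10% overall the bias is about 0.01 to 0.03 SD in absolute size.

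Four stronger readings are tempting, and the documents do not support them.

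- *The C contrast is certainly understated.* The sign depends on the mechanism, and unadjusted change scores overstate it when dropout depends on observed activity.
- *Randomised participants are being lost for want of a valid baseline.* This is possible but not shown. Accelerometer wear precedes randomisation, and randomisation is stratified by baseline activity, although the article does not say that four valid days are required before allocation or how the stratifier is measured.
- *Unblinded analysts will choose who counts.* The article does say "Neither study participants nor data analysts will be blinded to group allocation", but the hours, days and count cut-points are fixed in Outcome measures, and nothing leaves valid wear to the analysts' discretion.
- *Differential loss will be invisible.* The article commits to CONSORT reporting and to daily tracker recording, so losses by arm will be seen.

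The absence of a missing-not-at-random sensitivity analysis is no fault of this article; it can sit in the SAP.

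**Conclusion.** The point holds as a false general claim joined to an ambiguous model. Intention-to-treat on all randomised participants does not avoid the effects of dropout, and the mixed model without imputation is valid only under missing at random. Read literally, the analysis leaves out about 6 to 18 of 180 participants at the planned attrition. If dropout depends on observed activity and is higher in A than in C, unadjusted change scores favour C at 18 months by about 0.03 SD at 15% versus 5% loss and 0.08 SD at 40% versus 15%. That part can be avoided. If dropout depends on unobserved activity, a bias against C of 0.01 to 0.10 SD across the same splits remains whichever form is fitted, and keeping baseline in the model does not reduce it. All bias figures rest on assumed arm-specific losses, an assumed dependence of dropout on activity, and correlation 0.5. The wording and the model statement should be changed.

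**What to change.** 1. State that the linear mixed model is fitted to time in moderate and vigorous activity at baseline, 6, 12 and 18 months, with baseline as one of the responses and a common baseline mean across arms. Report the group-by-time contrasts. Every participant with any valid wear then contributes.
2. Replace the claim that the analysis avoids the effects of dropout with a statement that the comparisons are valid if data are missing at random.

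Both are changes of wording and model specification on data already planned. They need no extra visits or participants, and about a day of programming at most.

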### Sample size

The sample size is based on the number of participants needed to detect significant longitudinal changes in PA level. With a statistical power of 0.80, an alpha value of 0.05, a moderate correlation (*r* = 0.5) between measures, and an expected 10% attrition, a total sample size of 180 participants (60 per group) is required to detect a medium effect size (*d* = 0.53) (21). Calculation was performed by a statistician.

## Discussion

The ONWARDS study aims to explore longitudinal changes in PA, long-term exercise maintenance, health and implementation outcomes among inactive adults using three different digital interventions for PA promotion, namely an activity tracker with the personalized metric PAI, home-based online training *via* Les Mills+ and peer support *via* a Facebook closed-group. Inactive adults often do not access a training facility or use equipment for home exercise. A control group receiving “standard care” was therefore deemed to be unfair for these individuals. All participants in this study will therefore be provided with at least an activity tracker. The presence of three interventional groups will allow testing of which combination of strategies is more effective in increasing PA levels and maintaining them over the long-term.

Psychological factors, including lack of motivation and lack of skills/knowledge, represent a major barrier to PA (9, 10). Perceived self-efficacy can affect both motivation and actions and is important for lasting changes in PA (47). Other effective behavior change techniques used in mobile apps for PA include goal setting, monitoring and feedback about whether or not one gets enough exercise (13). PAI is personalized metric based on heart rate data which can be used by everyone of all ages and fitness levels. The PAI Health mobile app sets a clear goal, which is to keep a weekly PAI score above 100 for disease prevention and health promotion. Users who struggle with keeping physically active can self-monitor their PA level *via* the PAI Health app, which provides a daily feedback on their current PAI score and reminds them to try to reach their goal. Thanks to these features, we expect that the participants in this study will increase their perceived self-efficacy, competence and motivation for exercise which, in turn, might result in higher PA levels and better adherence to PA recommendation.

Geographical isolation and related environmental factors (e.g., lack of facilities) are especially related to health disparities and inequality in PA (48). Access to training facilities can promote PA with equipment for strength and aerobic exercise as well as group-based classes, which are motivating and result in better long-term adherence (29). However, many people do not have access to these facilities, and others have concerns about their appearance (10). Adverse weather conditions represent another major barrier to participation in PA, and high or low temperatures, rain, snow or wind may all decrease the pleasure derived from outdoor activities (49). Lack of time is one of the most reported reasons why healthy adults do not participate in sport or physical recreation (10, 50). Northern Norway, where this study will be conducted, is a region characterized by frequent adverse weather conditions as well as a high peripherality, with several people living outside urban areas and without easy access to training facilities. Moreover, study participants will be inactive young or middle aged adults, which most likely will be studying or working and might therefore perceive lack of time as a barrier to PA. The possibility for participants in groups B and C to exercise conveniently from home supported by video programmes has the potential to empowering them to perform regular PA while addressing common issues such as lack of time or concerns about appearance. Moreover, interventions with a group atmosphere, such as Les Mills+ online programmes, can be more effective in increasing engagement over time and reducing perceived stress (20).

The lack of social support is another common barrier to PA (10). Poor adherence to home-based exercise (24), in addition to the poor adherence observed in e-health interventions (51), makes the implementation of digital technologies for PA a challenging issue. Novel strategies are needed to ensure adherence to PA among adults and maintenance of behavior change (27). Social media are nowadays widely used in many people's daily routines and are shown to be valuable for targeting lifestyle change among young adults (28). In a study examining the efficacy of a Facebook social support group to increase PA in young women, participants in a Facebook social support group increased the number of steps per day more than those in the standard walking intervention (30). Participants in group C will be offered peer support *via* a Facebook closed-group, where they will have the possibility to share their experiences or ask for advice from other members of the group, as well as receive educational information about PA, motivational support and rewarding messages from the project team. It is expected that peer-support *via* social media will result in better adherence to PA, better maintenance of PA levels over the long-term, as well as fewer dropouts.

This study can contribute to reduce disparities in PA levels among inactive adults by increasing access to PA and promoting long-term adherence. Increased PA might, in turn, result in better prevention of lifestyle diseases. Digital interventions delivered at home can become an alternative to training facilities, making PA accessible and feasible for inactive populations and overcoming known barriers to PA. If effective, such interventions could potentially be offered on a large-scale through national health portals to all citizens who do not meet the minimum recommendations on PA. Effective e-health interventions for PA could also be prescribed by general practitioners or specialists to both healthy and impaired individuals. The study will be conducted in the Troms and Finnmark county in Northern Norway. However, the results will be applicable to other regions and countries. The interventions could be also applicable to selected patient groups, particularly those with mobility impairment characterized by low levels of PA.

## Ethics statement

The studies involving human participants were reviewed and approved by Regional Committee for Medical and Health Research Ethics (66573/REK nord). The patients/participants provided their written informed consent to participate in this study.

## Abbreviations

PA: physical activity
PAI: Personal Activity Intelligence
RCT: randomized controlled trial
SPIRIT, Standard Protocol Items: Recommendations for Interventional Trials
MET: metabolic equivalent
VO_2max_: maximal oxygen uptake
BMI: body mass index
SF-12: 12-Item Short Form Survey
PCS: perceived competence scale
SEE: Self-Efficacy for Exercise Scale
SSES: Social Support and Exercise Survey
SUS: System Usability Scale.
